### Delivering the modeling experiment

The experimental materials will be delivered by post. The experiment will be embedded within a questionnaire survey which will be administered twice, once before the intervention and once immediately following the intervention. Based on our previous experience, we plan that subjects will receive a letter of invitation, a set of instructions, and individually packaged set of materials for measuring behavioural simulation and intention that they will be asked to read in this order. On the second administration of the survey, they will also receive the intervention which they will be asked to complete prior to completing the process and outcome measures. Two reminders will be mailed to non-responding clinicians. Given our experience of the response rate in our previous study [31], we plan to offer a £10 incentive to each subject to increase response rates [33,34].

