### Work leading up to this protocol

#### Using psychological theory to identify salient beliefs that precede the behaviour (empirical antecedents)

We have conducted a number of preliminary studies to investigate the feasibility of using psychological theories in implementation research, and their ability to identify variables that might be targets for interventions. One of these forms the basis of this protocol - a study using the theory of planned behaviour to investigate factors associated with prescribing antibiotics for patients with uncomplicated sore throat by general practitioners (GPs) in Grampian [21]. Literature reviews, non-participant observation, and interviews with GPs were used to develop questionnaires that were distributed to a one in two random sample of GPs in the region, achieving a 70% response rate. Using the theory, we explored the relationships between GPs' perceptions and the strength of their intention to prescribe antibiotics. This allowed us to:

1. Identify whether GPs intended to prescribe antibiotics or not. The majority indicated that they intended to prescribe for less than half of patients presenting with uncomplicated sore throat in the next two weeks.

2. Estimate the overall impact of individual beliefs and perceptions on the strength of their motivation to prescribe; potentially modifiable beliefs accounted for 48% of the variance in GPs' intentions to prescribe.

3. Identify which beliefs had the biggest impact on intention to prescribe antibiotics.

4. Identify discriminant beliefs distinguishing GPs who intended to prescribe from those who did not.

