### Interventions

Our previous work [21] has identified eight discriminant beliefs that distinguish between GPs who do (intenders) and do not intend (non-intenders) to prescribe antibiotics for patients with uncomplicated sore throat (Table 2). We will make the assumption that altering these beliefs will change intentions to manage URTI without prescribing antibiotics, and we will therefore design the interventions to change these beliefs. Therefore, it will be possible to test the assumption empirically by applying a mediational analysis to explain intervention effects. Two theory-based interventions that incorporate behaviour change technologies will be designed to promote the management of URTI presenting in primary care without prescribing antibiotics.

**Table 2 T2:** Discriminant beliefs that distinguish between GPs who do (intenders) and do not intend (non-intenders) to prescribe antibiotics for patients with uncomplicated sore throat.

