### Process measurement

We will examine whether the interventions affect the discriminant antecedents identified in the previous theory of planned behaviour study (Table 2). We have piloted these methods successfully [29,31]. The results will be explored using the Baron and Kenny methodology for mediational analyses [32], which incorporates the Sobel test, to ascertain the extent to which these antecedent beliefs mediated effects on outcomes within these experiments. Where possible, the measurement will be made twice, with these process measures assessed both before and following the intervention. The time between measurements will be six to eight weeks.

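### Baseline measurement of the eight beliefs is intended but not secured, so the planned mediation analysis could overstate how far belief change explains the intervention effects

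*Protocol article*

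**What the plan says.** The Interventions section assumes that altering the eight beliefs in Table 2 will change intention, and says that "it will be possible to test the assumption empirically by applying a mediational analysis to explain intervention effects". That analysis is therefore the stated test of the protocol's theoretical assumption.

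The Process measurement section names the method: "The results will be explored using the Baron and Kenny methodology for mediational analyses [32], which incorporates the Sobel test". On timing it says: "Where possible, the measurement will be made twice, with these process measures assessed both before and following the intervention". It then adds, without the hedge, "The time between measurements will be six to eight weeks".

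The Delivering the modeling experiment section says that the survey is "administered twice, once before the intervention and once immediately following the intervention". It describes the pack as an "individually packaged set of materials for measuring behavioural simulation and intention that they will be asked to read in this order". Of the second survey it says that "they will also receive the intervention which they will be asked to complete prior to completing the process and outcome measures". This is the only place in that section where process measures are mentioned.

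Sample size and analysis gives analysis of covariance for comparing groups adjusted for baseline performance. No section states a baseline adjustment for the mediation models.

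**The concern.** The mediation analysis has three links: intervention to belief, intervention to outcome, and belief to outcome. Randomisation protects the first two. It does not protect the third, because GPs are not randomised to their beliefs.

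The beliefs were chosen because they already separate GPs who intend to prescribe from those who do not. Some association between belief and intention is therefore expected even if changing a belief changes nothing. In the earlier study, "potentially modifiable beliefs accounted for 48% of the variance in GPs' intentions to prescribe" with no intervention at all. If beliefs and outcomes are both taken only after the intervention, in one mailing, this standing association enters the belief-to-outcome path. An intervention that shifts belief scores, and shifts intention by some other route, can then look as if it worked through the beliefs.

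At stake is the explanation of any effect, and hence which beliefs a later trial would target. The estimate of the effect itself is not at stake.

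**Working it through.** **What the text secures**

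| Item | First survey | Second survey |
|---|---|---|
| Intention and simulation | Listed in the pack | Yes, after the intervention |
| Eight beliefs | Intended under Process measurement, with a hedge; not listed under Delivery | Yes, after the intervention, with the outcomes |

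The order of belief and outcome items within the second survey is not stated.

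**How large the problem could be.** The plan gives no figure for the mediation analysis, so there is none to reproduce. The calculation below is an illustration.

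Inputs from the article: 200 GPs in all (two groups of 100 when one factor is compared), or 100 GPs (50 per group, one active group against control).

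Assumed inputs, not in the article:
- the true effect of belief on intention is zero;
- the intervention shifts belief by a = 0.5 SD and intention directly by 0.5 SD;
- belief and intention correlate at r within arm, through stable traits only;
- each measure correlates at s with its own baseline.

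Sobel test at two-sided 5%: z = ab / √(a²·SE_b² + b²·SE_a²), where b is the fitted belief-to-intention coefficient.

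*Post-only:* b = r, so the spurious indirect effect is 0.5r.

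*With baseline belief and intention as covariates:* the normal equations give b = r(1 − s)/(1 + s − 2r²).
- r = 0.3, s = 0.7: b = 0.09/1.52 = 0.059; indirect effect 0.03 SD, against 0.15 SD post-only.
- r = 0.5, s = 0.7: b = 0.15/1.20 = 0.125; indirect effect 0.06 SD, against 0.25 SD.
- r = 0.69, s = 0.7: b = 0.207/0.748 = 0.277; indirect effect 0.14 SD, against 0.345 SD.
- r = 0.69, s = 0.8: b = 0.138/0.848 = 0.163; indirect effect 0.08 SD.

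Simulated share of trials declaring mediation (s from 0.7 to 0.8, at least 2,000 runs per setting):

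| n | r | Post-only | Baseline-adjusted |
|---|---|---|---|
| 200 | 0.3 | 87-89% | 6-11% |
| 200 | 0.5 | 92-94% | 15-36% |
| 200 | 0.69 | about 94% | 57-97% |
| 100 | 0.3 to 0.5 | 37-66% | 3-12% |

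Repeated runs of the least favourable r = 0.5 setting (n = 200, s = 0.7) gave 32-36%, so about a third.

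The post-only rates level off at the power to detect the belief shift. For a 0.5 SD shift, 0.5·√50 − 1.96 = 1.58 gives 94% with 100 per group, and 0.5·√25 − 1.96 = 0.54 gives about 70% with 50 per group.

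**Where adjustment helps less** (n = 200, same shifts)
- One shared trait with low stability (r = s): at 0.3 the rate falls only from 87% to 57% (0.15 to 0.09 SD), and at 0.5 from 93% to 88% (0.25 to 0.12 SD).
- Shared same-sitting error of 20% of variance, no shared trait: 57% before and after adjustment (0.10 SD both times).
- Shared trait 30% plus same-sitting error 20%: 92% before, 95% after (0.25 to 0.21 SD).

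**Where the problem does not arise**
- No shared cause of belief and outcome: about 2%.
- Intervention does not move the belief: at most about 4%.

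**The case against.** A reader might infer that the beliefs will be measured only after the intervention. The text does not support that. Process measurement plans both occasions and fixes the gap between them, and the second survey can be read as the first survey with the intervention added. A short list of pack contents does not prove that belief items are absent at baseline. This stands. What remains is that the hedge leaves baseline measurement open and the delivery section does not close it.

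A reader might also infer that a finding of mediation is close to certain. It is not. It needs the beliefs to move and a shared cause to exist, and with 100 GPs the illustrated post-only rates are 37-66%. The shifts and stabilities are assumptions.

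Nor does the 48% give a belief-intention correlation of √0.48 = 0.69. It is the joint contribution of a set of beliefs, so 0.69 is a multiple correlation, and the article does not say that the set is the eight in Table 2. It serves here only as an upper illustration.

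Covariates for the mediation models may properly be left to an analysis plan that is not shown, so their absence alone is no fault. But no plan can adjust for baseline beliefs that were not collected, and timing is something the article itself sets out.

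Finally, the analysis is described as exploratory, and confounding of mediator and outcome is a general limit of mediation analysis. Both are true and limit the weight of the point. Yet the Interventions section gives this analysis the task of testing the causal assumption.

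**Conclusion.** The point holds in a limited form. Baseline beliefs are intended but not secured, and the two sections on timing and delivery do not agree clearly. If only post-intervention beliefs were analysed, the Sobel result could overstate mediation. For assumed correlations of 0.3 to 0.5 with stability of 0.7 to 0.8, baseline covariates cut false mediation from 87-94% to between about 6% and one third with 200 GPs, and from 37-66% to about 12% or less with 100. These sizes rest on zero true mediation and direct shifts of 0.5 SD in both belief and intention.

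Baseline adjustment reduces the bias from stable differences between GPs. It does not remove error shared by measures completed together, and its benefit shrinks when the correlation is high or stability is low. The randomised comparisons of intention and simulation are not affected. The change is worth making before the first mailing, because baseline beliefs cannot be recovered once the intervention has been sent.

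**What to change.** 1. In Process measurement, remove the hedge so that beliefs are rated before and after the intervention for every GP. In Delivering the modeling experiment, list the eight belief items in the first survey pack.
2. State that the mediator model and the outcome model will include baseline belief and baseline intention (or baseline simulation, when that is the outcome).
3. State that confounding of belief and outcome, including error from completing both in one sitting, may remain, so a positive mediation result supports the assumption but does not prove it.

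The cost is eight rating items in a survey that is already being posted, plus two covariates per model. The downsides are a slightly longer first questionnaire and exposure of all arms to the belief items six to eight weeks before the intervention.

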### Sample size and analysis

In a 'definitive trial', there is inherent variability in the number of patients who consult with each condition, and the characteristics of these patients vary from doctor to doctor and from year to year. By giving all subjects in the experiment the same context in which to examine behavioural intention, we have eliminated these two sources of variation. Therefore, if we use the same outcome in both the trial and in the IME, we would expect its standard deviation to be smaller in the IME than in the trial. Thus, a given shift in outcome (difference between two groups) represents a much larger effect size (difference in outcome divided by the standard deviation) in the IME than in the trial. Thus, if a trial were to produce a moderate effect size we might expect a large effect size in the IME. The IME will be powered to detect difference between each of the active intervention groups and the control group. Using standard methods for a continuous outcome, we need 50 subjects per group to have 80% power of detecting an effect size of 0.8 using a significance level of 2.5%, giving a total sample size of 200 for the experiment. We will over-sample, using an initial sample of 800, to ensure that we achieve this final sample size. This will be adjusted in the light of the impact of the incentive. Groups will be compared using methods appropriate for comparing independent samples (t-tests to compare two groups, analysis of covariance to compare groups adjusting for differences in baseline performance).

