### Design

Two interventions will be developed to address the discriminant beliefs in the prescribing of antibiotics for sore throat. Appropriate intervention components will be selected from a number of available evidence-based behavioural technologies. The design of the interventions will incorporate these techniques and will be further informed by the empirical findings of our previous studies. The interventions will be evaluated in a 2 × 2 factorial randomised controlled trial delivered in a postal questionnaire survey.

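### The 2 × 2 factorial trial is powered on single-cell versus control contrasts, each using only half of the 200 GPs planned for the final sample

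*Protocol article*

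**What the plan says.** The Design section of the Methods fixes the structure: "The interventions will be evaluated in a 2 × 2 factorial randomised controlled trial delivered in a postal questionnaire survey". The Abstract says the same. Under Sample size and analysis the powered comparison is: "The IME will be powered to detect difference between each of the active intervention groups and the control group". The size follows: "we need 50 subjects per group to have 80% power of detecting an effect size of 0.8 using a significance level of 2.5" per cent, "giving a total sample size of 200 for the experiment". To reach it, 800 GPs are to be approached.

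The analysis is described only as a comparison of groups by methods for independent samples: "t-tests to compare two groups, analysis of covariance to compare groups adjusting for differences in baseline performance". The text does not say whether these groups are the four cells or the two margins of each factor. It does not mention main effects, pooling over the other intervention, or an interaction, and it gives no reason for preferring cell contrasts.

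**The concern.** A 2 × 2 factorial lets every participant contribute to the estimate of both interventions. A contrast of one active cell with the control cell gives that up. It answers a narrower question, the effect of one intervention when the other is absent, with half the data.

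This matters for the second aim, which is to find the interventions with the largest impact on intention and simulated behaviour. That is a task of estimating and ranking, so precision counts beyond passing a test at 0.8. The 0.8 itself is an expectation argued from smaller variability in the experiment than in a definitive trial, and it is not a measured value. If the true effect is moderate, the choice of contrast largely decides whether it is found.

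The powered contrast sets the sample size. An analysis plan that used the margins would no longer match the stated power basis, and one that followed it would lose the precision. Either way the section needs rewording.

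**Working it through.** **Inputs.** From Sample size and analysis: 50 per group, total 200, effect size 0.8 (SD = 1), power 80%, significance level 2.5%. From Design: four cells. Assumptions: two-sided test (sidedness is not stated), equal cells, no interaction unless noted, no baseline adjustment.

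**What a group is.** 4 × 50 = 200, so a group is a cell. A cell v control contrast uses 50 + 50 = 100 of 200.

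**The plan's own figure.** n per group = 2(z₀.₉₈₇₅ + z₀.₈₀)² / 0.8² = 2(2.241 + 0.842)² / 0.64 = 29.7, so 30 (31 by the exact t-test). One-sided at 2.5% gives 25 (26). The stated 50 is not reproduced. It comes out if the power is about 95% (48; exact 49) or the effect size about 0.62 (50).

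**Power of the cell contrast at 0.8.** Φ(0.8/0.200 − 2.241) = Φ(1.759) = 96.1% (exact t 95.6%), against the stated 80%.

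**Cell against margin.**

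| | Cell v control (50 v 50) | Margin (100 v 100) |
|---|---|---|
| SE, in SD | √(2/50) = 0.200 | √(2/100) = 0.141 |
| Detectable effect at 80% power (exact t) | 0.62 | 0.44 |
| Power at 0.4 (exact t) | 39% | 72% |
| Power at 0.5 (exact t) | 59% | 90% |
| Power at 0.8 (exact t) | 96% | >99.9% |

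The variance ratio is 0.200² / 0.141² = 2. It does not depend on sidedness. Adjusting for baseline shrinks both standard errors by the same factor, so the ratio also survives analysis of covariance.

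**Interaction.** The SE of the interaction contrast is √(4/50) = 0.283 SD. The interaction detectable with 80% power at 2.5% is (2.241 + 0.842) × 0.283 = 0.87 SD. It can be estimated but not decisively tested.

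**When the margin stops being better.** Main effect = stand-alone effect + interaction/2. The margin test is the more powerful if main effect / 0.141 > stand-alone effect / 0.200, that is, if the main effect exceeds 0.707 of the stand-alone effect. This fails only when the interaction removes more than 2 × (1 − 0.707) = 59% of the stand-alone effect. At that point the main effect understates the stand-alone effect by 29%.

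**Significance level.** 2.5% fits 5% shared by two contrasts. Read literally, each active group against control means three contrasts, which sum to 3 × 2.5% = 7.5%. If only two are meant, the combined cell of 50 enters no powered comparison.

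**The case against.** The strongest reply is that sizing for cell contrasts is the more demanding choice and over-powers the main effects when there is no interaction. The stand-alone effect against control is also a legitimate target. Sub-additive effects are plausible here: both interventions address the same set of discriminant beliefs, the example intention item is bounded at 0 to 10, and in the earlier study most GPs already intended to prescribe for fewer than half of such patients. This stands as an argument that could be made for cell contrasts. The protocol does not make it, and reporting the interaction and cell differences would cover it.

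A reader might also infer that the trial will be analysed only by separate t-tests, that every estimate will use half the data, or that the interaction will never be examined. The document does not support this. It names analysis of covariance as well as t-tests, fixes no contrasts, and may leave the model to an analysis plan that is not shown. Naming analysis of covariance does not settle the matter, though. Fitted to all 200 with each active cell compared with control, it has essentially the same 50 v 50 precision. The choice of contrast decides, and the only contrast stated is cell v control.

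Finally, the 200 are the GPs planned for the final sample, not all those approached or necessarily all those randomised.

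**Conclusion.** The point holds as a mismatch between the factorial design and the contrast on which it is powered. Each powered contrast uses 100 of the 200 planned GPs, and absent interaction its variance is twice that of the margin contrast. These sizes assume a two-sided 2.5% test and equal cells. The margin test keeps its power advantage unless one intervention removes more than about 59% of the other's effect.

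It is tempting to conclude that the trial is underpowered. It is not: against its own target of 0.8 the cell contrast has about 96% power. The stated 50 per group is more than its inputs require, and this arithmetic should be corrected too. No bias or invalid test is shown. The loss is in precision and in clarity about what is estimated, so this is a should-fix point and not a must-fix one.

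**What to change.** Name as primary one linear model (analysis of covariance) per outcome on all analysed GPs, with terms for intervention 1, intervention 2 and the baseline value. Test each main effect at 2.5%; two such tests fit a 5% total and use all four cells. Report the interaction, from the same model with the product term added, with its confidence interval and as an estimate, given an SE of about 0.28 SD. Give the cell v control differences as supporting results.

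Restate the power for the contrast used: for main effects with 200 GPs, 80% power at 0.44. If the sponsor prefers the cell contrast, the protocol should say so, give the reason, state how many contrasts share the significance level, and correct the 50 per group or its inputs.

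The cost is wording only, with no new recruitment or data. The drawback is that under a negative interaction the main effect understates what an intervention does alone. The interaction estimate and the cell differences would show this.

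### The sample-size figures do not agree with each other: the stated inputs give about 31 per group (26 if one-sided), not 50, and the discrepancy is on the safe side

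*Protocol article*

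**What the plan says.** All the figures are in the protocol article, under Sample size and analysis.

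- **Comparison powered:** "The IME will be powered to detect difference between each of the active intervention groups and the control group".
- **Method:** "Using standard methods for a continuous outcome". The same section names t-tests for comparing two groups, with analysis of covariance to adjust for baseline.
- **Effect size:** 0.8, where the section defines the term as the difference in outcome over its standard deviation.
- **Result:** "we need 50 subjects per group to have 80% power of detecting an effect size of 0.8 using a significance level of 2.5"%. Four such groups make up the overall target, the article says, "giving a total sample size of 200 for the experiment".
- **Non-response:** "We will over-sample, using an initial sample of 800, to ensure that we achieve this final sample size".

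The section does not say whether the 2.5% level is one- or two-sided, and it describes no further allowance inside the figure of 50. The Design section describes the study as a 2 × 2 factorial trial, hence four groups.

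**The concern.** The article gives a complete calculation: outcome type, standardised effect, power, significance level, comparison and answer. Only the sidedness is missing. A standardised effect of 0.8 is large, and 50 per group looks too many for 80% power at that effect, even at a 2.5% level.

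The sentence is the article's account of what the experiment can detect, and the target of 200 is the figure that the initial sample of 800 is meant to secure. If the inputs are right, the target exceeds what they require. If 50 is right, then the power, the effect size, the level or the comparison is misreported. Either way, the sentence gives a wrong picture of the experiment's sensitivity.

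**Working it through.** **Inputs** (all from Sample size and analysis): effect size d = 0.8, so SD = 1; power 80%; level 2.5%, tried both ways; two independent groups of equal size; stated answer 50 per group.

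**1. Attempt to reproduce 50.** The normal approximation is n per group = 2(z_alpha + z_power)² / d², with z_power = 0.8416.

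- Two-sided 2.5%: 2 × (2.2414 + 0.8416)² / 0.64 = 29.7, so 30. The t-test (noncentral t) gives 30.99, so 31.
- One-sided 2.5%: 2 × (1.9600 + 0.8416)² / 0.64 = 24.5, so 25. The t-test gives 25.52, so 26.

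The stated figure is not reproduced either way. Against 31, it is larger by a factor of 50/31 = 1.61. Four groups would total 4 × 31 = 124 (two-sided) or 4 × 26 = 104 (one-sided), not 200.

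**2. What 50 per group delivers.** The standard error of a difference in SD units is √(2/50) = 0.2, so d = 0.8 lies 0.8/0.2 = 4.0 standard errors from zero.

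| Level 2.5% | Power for 0.8, normal | Power for 0.8, t-test | Effect detectable with 80% power, t-test |
|---|---|---|---|
| Two-sided | Φ(4.0 − 2.2414) = 96.1% | 95.6% | 0.62 SD |
| One-sided | Φ(4.0 − 1.9600) = 97.9% | 97.7% | 0.57 SD |

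**3. Could another standard route give 50?**

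| Variant (d = 0.8; 80% power unless stated) | n per group or cell | Agrees with the text? |
|---|---|---|
| Level halved again (1.25% two-sided) | 35 normal, 37 t-test | No: not 50, and the text gives 2.5% |
| Level divided by three (0.83% two-sided) | 38 normal, 40 t-test | No: not 50, and the text gives 2.5% |
| Allowance for a nonparametric test | 33 (31/0.955) to 37 or 38 (32/0.864 = 37.04) | No: not 50 |
| Factorial main effect, two-sided 2.5% | (2.2414 + 0.8416)² / 0.64 = 14.9, so 15 per cell | No: not 50 |
| Power 95%, two-sided 2.5% | 48 normal, 49 t-test | Near 50, but the text says 80% |
| Effect size 0.62, two-sided 2.5% | 50 normal, 51 t-test | Yes in size, but the text says 0.8 |
| Interaction contrast of 0.8 SD, one-sided 2.5% | 4 × (1.9600 + 0.8416)² / 0.64 = 49.06, so 50 per cell | Yes in size, but the text names active against control |
| Interaction contrast of 0.8 SD, two-sided 2.5% | 59.4, so 60 per cell | No |
| 36% loss applied to 32 | 32/0.64 = 50 | Yes in size, but no such allowance is described |

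Every route to about 50 changes a stated input or adds one that the article does not mention. Baseline adjustment by analysis of covariance would lower the required number, not raise it.

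**The case against.** The strongest defence is that nothing is harmed. At 50 per group the experiment exceeds its 80% power target for 0.8, the type I error is untouched, and no planned comparison becomes invalid. The practical cost is at most some extra GPs answering a postal questionnaire in a modelling-phase study. That stands, and it limits how serious the point is.

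A second defence is that the 50 may have a legitimate origin that the article compressed away. An interaction contrast does give 50 per cell at a one-sided 2.5% level, and 95% power gives 49 per group. This is a fair warning against assuming which figure is wrong. It does not rescue the sentence, which names a different comparison and a different power. Nor does attrition explain the gap on the text as written, since the mailing of 800 is what is meant to cover non-response and 200 is the final sample.

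Two stronger readings are tempting, and the document supports neither:

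- **That the stated power or the stated effect size is the error.** The mistaken item could equally be the number per group, the comparison, or an allowance that is not described.
- **That a null result would be dismissed as uninformative for effects below 0.8.** The article says nothing of the kind. A non-significant result is properly read from its estimate and confidence interval, which depend on the achieved sample and the observed SD, not on the planning sentence.

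**Conclusion.** The point holds as an internal inconsistency. For active against control, with effect size 0.8, 80% power and a 2.5% level, about 31 per group are needed two-sided or 26 one-sided, not 50. The gap is too large to be rounding or a choice between the normal and t calculations. It is conservative: with 50 per group, power for 0.8 is about 96% two-sided (98% one-sided), and the effect detectable with 80% power is about 0.62 SD (0.57 one-sided).

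This rests on equal groups, a common SD, an unadjusted two-sample comparison and a final sample of 200. It does not depend on which sidedness was meant, because neither reading gives 50. A reader might infer from a failed sample-size check that the experiment is too small; the arithmetic shows the opposite for the stated target. The sentence should be fixed, but the error does not threaten the validity of the experiment.

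**What to change.** 1. Retrieve the original calculation and establish which of the number per group, power, effect size, level or comparison was misreported, or whether an allowance was left out.
2. State whether 2.5% is one- or two-sided, and confirm which comparison is powered.
3. Restate the sentence so that the figures agree. If 50 per group and a two-sided 2.5% level are kept for active against control, it could read: with 50 per group (200 in total) and a two-sided 2.5% level, each comparison of an active group with control has about 96% power for an effect size of 0.8, or 80% power for about 0.62 SD.

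The effect size the authors regard as worth detecting should remain their choice. The 0.62 describes what 50 per group can detect and is not a new target. The cost is a look at the original calculation and one rewritten sentence; recruitment need not change.

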### Outcome measurement

Two outcome measures will be assessed, behavioural intention and behavioural simulation. We will measure behavioural intention using the standard methods used in investigations based on the theory of planned behaviour using rating scales of likelihood, frequency, or agreement with statements or questions about intention (*e.g*. Out of the next 10 patients you see with acute sore throat, how many do you intend to prescribe antibiotics for? Score 0 – 10). To measure behavioural simulation, participants will be asked to respond to written scenarios describing patients presenting with sore throat in general practice. The scenarios will reflect the range of patients and clinical features that present in general practice informed by qualitative work conducted in our previous work [21]. Participants will be asked to write on a simulated set of notes the relevant management they would use.

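### An unadjusted t-test and baseline-adjusted ANCOVA are both named for the group comparisons, with no statement of which gives the main result

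*Protocol article*

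**What the plan says.** All references are to the protocol article.

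- **Analysis** (Sample size and analysis). Groups are to be compared with methods for independent samples, given as "t-tests to compare two groups, analysis of covariance to compare groups adjusting for differences in baseline performance". Neither method is called primary, and no condition is given for using one rather than the other.
- **Contrasts and size** (same section). The experiment is powered for each active group against control: "we need 50 subjects per group to have 80% power of detecting an effect size of 0.8", at a significance level of 2.5%, with 200 subjects in total. Sidedness is not stated, and no baseline correlation enters the calculation.
- **Outcomes** (Outcome measurement). "Two outcome measures will be assessed, behavioural intention and behavioural simulation".
- **Baseline** (Delivering the modeling experiment). The survey is to be "administered twice, once before the intervention and once immediately following the intervention". The mailing holds an "individually packaged set of materials for measuring behavioural simulation and intention". The second round differs in this way: "On the second administration of the survey, they will also receive the intervention". Baseline values of both outcomes are therefore planned.
- **Process measures** (Process measurement). A qualifier appears here: "Where possible, the measurement will be made twice, with these process measures assessed both before and following the intervention". It concerns the antecedent beliefs, not the two outcomes.

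**The concern.** Two analyses are available for the same contrast and nothing fixes which one counts. This matters in two ways.

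First, precision. In a randomised comparison the baseline score belongs in the model because it predicts the outcome, whether or not the arms happen to differ on it. A t-test on the follow-up scores leaves that information unused.

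Second, freedom of choice. The t-test and ANCOVA will sometimes fall on opposite sides of the significance threshold. If the choice is made after the results are seen, the 2.5% error rate no longer holds. The same freedom arises for each of two outcomes and for each active-versus-control contrast.

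**Working it through.** **Inputs.** From the article: 50 per group, effect size 0.8, significance level 2.5%, power 80%. Assumed: a two-sided test, and a baseline/follow-up correlation r of 0.3, 0.5 or 0.7. The article gives neither. Its two outcomes may also have different correlations.

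**1. The plan's own figure.** The usual formula is n per group = 2(z₁₋α/₂ + z₁₋β)²/d². With z values 2.241 and 0.842 this is 2 × 3.083²/0.8² = 29.7, so 30 (31 with the t distribution). A one-sided 2.5% test gives 25 (26). The stated 50 is not reproduced. That is a separate matter, but it bears on the size of this one: the trial has more room at 0.8 SD than the article says.

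**2. Unadjusted analysis at 50 per group.** The standard error in SD units is √(2/50) = 0.2.
- Detectable effect at 80% power: 3.083 × 0.2 = 0.617 SD (0.625 with the noncentral t).
- Power at 0.8 SD: Φ(0.8/0.2 − 2.241) = Φ(1.759) = 96.1% (95.6% with the noncentral t).

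**3. ANCOVA at 50 per group.** Adjustment multiplies the standard error by √(1 − r²).

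| r | √(1 − r²) | Cut in SE | Detectable effect, normal | Detectable effect, t | Power at 0.8 SD (normal) | Power at 0.5 SD (normal) |
|---|---|---|---|---|---|---|
| none (t-test) | 1 | 0 | 0.617 | 0.625 | 96.1% | 60% |
| 0.3 | 0.954 | 5% | 0.588 | 0.596 | 97.5% | 65% |
| 0.5 | 0.866 | 13% | 0.534 | 0.541 | 99.1% | 74% |
| 0.7 | 0.714 | 29% | 0.440 | 0.446 | 99.96% | 90% |

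The t column is 0.625 times the multiplier. The normal and t values differ by less than 0.01 SD, so the rounded figures 0.59, 0.54 and 0.45 are good to about that. The 0.5 SD column is not a target of the plan; it shows what happens if the true effect is smaller.

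**4. Cost of leaving the choice open.** 20,000 null trials were simulated for each r, with 50 against 50, normal scores and a two-sided 2.5% test. The simulation error on a rate of 2.5% is √(0.025 × 0.975/20,000), about 0.1 percentage points.

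| r | t-test alone | ANCOVA alone | Methods disagree | Either significant |
|---|---|---|---|---|
| 0.3 | 2.7% | 2.7% | 1.6% | 3.5% |
| 0.5 | 2.5% | 2.4% | 2.5% | 3.7% |
| 0.7 | 2.3% | 2.5% | 3.4% | 4.1% |

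Each method holds its level when used alone. The excess comes only from picking the favourable one.

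A rule that switches to ANCOVA only when the baselines differ at the 5% level gave error rates of 2.5%, 2.0% and 1.5%. Such a rule does not inflate error; in these runs it was conservative at the two higher correlations.

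**The case against.** The strongest reply is that baseline-adjusted ANCOVA, the remedy, already stands in the quoted sentence, and that ranking a main and a supporting analysis is often left to a full protocol or analysis plan, neither of which is shown here. Silence on the ranking would indeed be no finding. But the article is not silent: it assigns the unadjusted t-test to two-group comparisons, which is the form of every contrast it powers, and sets ANCOVA beside it. That is a choice fixed badly rather than a detail left out.

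Four further objections stand and limit the point.

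- A reader might infer that ANCOVA is reserved for the case where imbalance is seen. The text sets no such trigger; the phrase about baseline differences can simply describe what ANCOVA does.
- A reader might infer that the plan rests on t-tests and so gives precision away. Precision is lost only if the t-test decides, which the text does not say outright.
- The size of the gain rests on an assumed correlation. The article does not say that the same scenarios are used in both rounds, so for the simulation outcome the correlation could be low.
- Baseline scores for every analysed GP are the intention, not a certainty. They depend on response to the first postal survey, and the article expects non-response.

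**Conclusion.** The point holds as a lack of a designated primary analysis, in a design that plans to collect the covariate that would make the better analysis possible. It should be corrected, but it does not threaten the trial.

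A reader might go on to infer that the trial is underpowered without adjustment. The figures do not support that: at the stated 0.8 SD, unadjusted power with 50 per group is already about 96%, and adjustment lifts it only to between 97.5% and nearly 100%. The gain counts if true effects are smaller, since the detectable effect falls from about 0.62 SD to somewhere between 0.45 and 0.59 SD for correlations from 0.7 down to 0.3.

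The error rate of about 3.5% to 4.1% is what would follow from always reporting the significant method. Nothing in the article says this is intended; it only fails to rule it out. The results assume a two-sided test, 50 analysed per group and roughly normal scores.

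**What to change.** For each of the two outcomes, name one primary analysis: ANCOVA of the post-intervention score on randomised group plus the baseline value of the same outcome, used whatever the observed baseline balance. Estimate the planned active-versus-control contrasts from that model. Fitting the two intervention factors as main effects instead would replace those contrasts with different ones, so it should not come in as part of this change. Label the t-test as descriptive or supportive.

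The cost is a change of wording. The baseline measurement is already planned, and neither the sample size nor the survey materials need to change.
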